## Abstract

**Background:**

Previous studies have reported a high prevalence of chronic otitis media (OM) and hearing impairment (HI) in Aboriginal children in the Northern Territory (NT) of Australia. Children affected by these disorders are believed to be at increased risk for adverse outcomes in early childhood development, school attendance, academic performance, and child maltreatment and youth offending. However, to date, there have been no studies quantifying the association between HI and these outcomes in this population.

**Objective:**

This study will investigate the association between HI and the 5 outcomes in Aboriginal children living in remote NT communities.

**Methods:**

Individual-level information linked across multiple administrative datasets will be used to conduct a series of retrospective observational studies on selected developmental and school outcomes. The predictor variables for all studies are the results from audiometric hearing assessments. The outcome measures are as follows: Australian Early Development Census results, representing developmental readiness for school, assessed around 5 years of age; Year 1 school attendance rates; Year 3 school-based academic performance, assessed in the National Assessment Program—Literacy and Numeracy; incidence of child maltreatment events (including both notifications and substantiated cases); and incidence of a first guilty verdict for youth offenders. Confounding and moderating factors available for the analysis include both community-level factors (including school fixed effects, socioeconomic status, level of remoteness, and housing crowdedness) and individual-level factors (including maternal and perinatal health and hospital admissions in early childhood).

**Results:**

The study commenced in 2018, with ethics and data custodian approvals for data access and linkage. This has enabled the completion of data linkage and the commencement of data analysis for individual component studies, with findings expected to be published in 2019 and 2020.

**Conclusions:**

This study will provide first evidence of the impact of OM-related HI on the developmental, educational, and social outcomes of Australian Aboriginal children. The findings are expected to have significant implications for policy development, service design, and resource allocation.

**International Registered Report Identifier (IRRID):**

RR1-10.2196/15464

## Introduction

### Background

Children’s experiences during infancy and early childhood are critical to their health and educational and socioemotional well-being throughout their life course [1-5]. Through this period of rapid development, children are particularly sensitive to influences from their living environment [1,6]. At this age, the ability to hear is crucial to children’s normal development, as children learn to speak and communicate by imitating the sounds they hear, and hearing impairment (HI) is likely to reduce children’s exposure to sounds and voices and hamper their language development [7]. Consequently, delayed or impaired language learning can adversely affect children’s physical health, as well as social and emotional development [7-9].

Otitis media (OM) and the associated HI among Australian Aboriginal children has been extensively researched [10-19]. Community surveys conducted in Aboriginal children living in remote communities have consistently reported extremely high prevalence of OM, as high as 90% in some reports, which has persisted through decades of clinical and public health interventions [14,18-20]. Studies have also found that OM affects Aboriginal children early in life, is more severe, and persists for longer [7,10,21], with prevalence peaking at the young age of 5 to 9 months [15]. Among the affected children, if OM is left untreated or not treated adequately, it often progresses to chronic suppurative OM (CSOM) and tympanic membrane perforation, with mild to moderate conductive hearing loss [22-24]. The impact of HI on language development may be compounded in Aboriginal children, when English is a second or third language, but school-based teaching relies on English [22,25-28]. In this setting, it may be reasonably expected that OM-related HI may directly or indirectly impact children’s readiness for school and subsequent participation and performance at school, as well as their ongoing social and behavioral development through childhood and adolescence.

Although there is an abundance of the literature showing the correlations among child maltreatment, youth offending, early childhood development, school performance, and school attendance [29-33], to date, there has been no population-level investigation into the impact of HI on the long-term developmental, educational, and social outcomes of Aboriginal children. Furthermore, studies investigating the impact of OM (or its associated HI) on various aspects of early childhood development, including cognitive development, speech and language development, and educational outcomes, have produced equivocal results [7,34-36]. Several reasons have been proposed for such an inconclusiveness [22,34-37]. First, there are limitations in study design. Many studies have relied on surveys and have therefore been restricted by the inherent limitations of this design, as well as limited statistical power. On the other hand, the negative associations of OM with effusion (OME) and children’s later language development found in some prospective and randomized clinical trials still need to be verified with large-scale studies that can provide more precise population-level estimates. Second, the majority of these studies used clinical diagnoses of OM, such as OME [38] or chronic OM [39,40] as the independent variable, rather than a direct assessment of hearing. The uncertainty surrounding the presence and degree of HI when OM is used as the predictor variable compromises the validity of the findings. Third, many studies have not controlled for known confounding or moderating variables, such as maternal education and socioeconomic status [41-44]. Finally, there has been a lack of population-level audiometric assessment data to report population-level outcomes.

### Objectives

To address this research gap, the Hearing Loss in Kids (HeLoKids) Project aims to apply a life-course epidemiological approach [45] to investigate the association between HI and developmental, educational, and social outcomes in Aboriginal children living in remote Northern Territory (NT) communities. By using linked administrative datasets containing longitudinal unit-record data for health, education, child protection, and youth justice systems, as well as hearing assessment results, this study is able to examine the selected outcomes while controlling for a wide range of potential confounders and moderators, as illustrated in the conceptual model in Figure 1.

Specifically, the study will undertake a series of studies that test the following hypotheses:

HI is independently associated with poorer developmental outcomes at the time of entry into full-time school (aged about 5 years).HI is independently associated with lower school attendance rates in Year 1 (aged about 6-7 years).HI is independently associated with poorer academic achievements in Year 3 (aged about 8 years).HI is independently associated with higher risk of child maltreatment.HI is independently associated with higher risk of youth offending.

**Figure 1 figure1:**
[figure not shown]
Conceptual diagram indicating the pathways of influence of hearing impairment on life trajectories and the interplay between them (SES: socioeconomic status).

## Methods

### Setting

The NT is located in the north and central part of Australia, with an area of 1,352,176 square kilometers. It has the smallest total population among Australian states and territories, with an estimated resident population of 247,300 in 2018 [46], and the highest proportion of Aboriginal people in the total population (about 30%, compared with 3% for Australia) [47]. The NT also has the highest proportion of the total population living in remote and very remote areas (40.4% in 2017), as measured using the Accessibility and Remoteness Index of Australia (ARIA+) [48,49]. NT Aboriginal people have also been reported to be socioeconomically disadvantaged, as measured with the Socio-Economic Indexes for Areas, based on aggregated Australian population census data on social and economic status [50]. In addition to the high prevalence of OM, NT Aboriginal children have lower school attendance and retention, lower academic achievement, higher rates of reported child maltreatment, and higher rates of youth offending than their non-Aboriginal counterparts [51-55].

### Design and Linkage Process

The HeLoKids Project will be conducted as a series of retrospective observational cohort studies to examine the association between HI and a range of developmental, educational, and social outcomes. These studies will utilize administrative datasets held within an extensive repository of deidentified unit-level information for NT children, which has been incrementally developed since 2009 [56]. SA NT DataLink (a South Australia [SA] and NT partnership) [57] completed the linkage of datasets collated in the repository. The data linkage process involves individual data custodians preparing a dataset containing identifying information only and then forwarding the dataset to SA NT DataLink. SA NT DataLink then combines the datasets from multiple custodians and links records for the same individual, which are present in the various datasets, and creates an anonymized project-specific linkage key for each individual. SA NT DataLink then adds the linkage key to the original datasets and returns each dataset to the respective data custodian. The data custodian creates a research dataset by combining the linkage keys with approved research variables and removing identifying information. The research dataset, created by each custodian, is then forwarded to the research team. The research team is able to use the linkage keys to merge information on individuals from multiple datasets to create the datasets necessary for analysis.

### Remote Hearing Assessment Dataset

The Remote Hearing Assessment (RHA) dataset contains middle ear examination and audiometric assessment information collected by the NT Outreach Hearing Health Program [58]. This program is an Australian Government funded specialist ear and hearing health outreach service, available to all NT Aboriginal children and young people, aged under 21 years, most of whom live in remote communities.

The NT Outreach Hearing Health Program uses pure tone audiometry to assess children’s hearing ability and determine the type (sensorineural, conductive, mixed, or indeterminate) and level of hearing loss. The level of hearing loss of an ear is calculated by taking the average of the thresholds of hearing (as deviation from normal threshold, in decibels Hearing Level—dB HL) for 3 frequencies: 500 Hz, 1000 Hz, and 2000 Hz. The results for each ear are classified as either normal or 1 of 4 ordinal categories of hearing loss, namely mild (16-30 dB HL), moderate (31-60 dB HL), severe (61-90 dB HL), and profound (91 dB HL or greater). This relatively conservative classification of hearing loss was chosen over the more widely used World Health Organization classification, as it is deemed more suitable for children aged under 15 years [58,59]. Further details on this classification of hearing loss are available elsewhere [58]. The clinical assessment for each ear is also recorded and classified under the following categories: acute OM (AOM), AOM with perforation, CSOM, dry perforation, Eustachian tube dysfunction, increase in middle ear pressure, OME, normal, and others.

The dataset provided to this study includes information collected from 2007 to 2015, for over 8000 children and young people aged between 0 and 21 years, which is about 22% of the NT Aboriginal population in this age group. Children and young people access these services through referral by primary care services. From January 2013, access to these services was prioritized according to clients’ need for service. This means that the children and young people whose records are captured in the RHA dataset are not a random sample of the general population, and the information is likely to be biased toward those with abnormal middle ear examination and hearing difficulties.

### The Study Cohort

The study cohort comprises NT-born Aboriginal children, with hearing assessment results in the RHA dataset and with a residential location classified as *remote* or *very remote* on the basis of ARIA+ [48]. Further inclusion and exclusion criteria will vary among the component studies of this study, depending on the respective requirements. In principle, as the data analysis will be based on a complete-case analysis, only children with data in the selected dependent, outcome, and control variables will be included. Children who have had surgical treatment for OM before the age of 4 years will be excluded, as the surgery could alter the impact of HI during the early childhood period. This will be done by searching in another linked administrative dataset, the NT Hospital Separations Dataset, and excluding children admitted before the age of 4 years, with any diagnosis code plus any procedure code related to OM and its treatment (Table 1).

**Table 1 table1:** Otitis media—related hospital admission diagnoses and surgical procedures used to exclude children who had received surgical treatment, with International Classification, 10th Revision-Australian Modification codes.

ICD-10AM^a^ Code		Diagnosis/procedure

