### Dependent Variables

For this study, the term “hearing loss” (HL) is used for a single ear to refer to a certain degree of loss of hearing ability, whereas “hearing impairment” (HI) is used for an individual’s state of hearing loss in both ears. The dependent variables used across all component studies will be HI, and its values will be derived from the hearing assessment data contained in the RHA dataset. It will be an ordinal variable comprising the following categories:

Normal hearing: normal audiometry results in both ears.Unilateral hearing loss: normal in one ear and any degree of hearing loss in the other.Mild HI: mild hearing loss in the better hearing ear.Moderate-or-worse HI: moderate-or-worse hearing loss in the better hearing ear.

Although OM tends to develop early in life in NT Aboriginal children and be persistent and often asymptomatic [19,21], a child may not have a hearing assessment until the child is older, when both the diagnosis of OM and hearing assessment become easier. As a result, a proportion of children may not be tested until after the outcome event for the study. There are also a proportion of children with multiple records of hearing assessment in the RHA database. For the purpose of this study, we assume the results for the first hearing assessment of a child, at any age, are representative of the long-term hearing level for that child.

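### The surgery exclusion stops at age 4 and ignores the date of the hearing test, and pooling all types of loss supports a conclusion on HI of any cause, not OM-related HI

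*Protocol article*

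**What the plan says.** **Surgery.** The Study Cohort section states: "Children who have had surgical treatment for OM before the age of 4 years will be excluded, as the surgery could alter the impact". The period it has in mind is early childhood. The rule is applied by searching hospital records: "excluding children admitted before the age of 4 years, with any diagnosis code plus any procedure code related to OM and its treatment", with the codes listed in Table 1. The date of the hearing test plays no part in it. The section adds that further criteria will differ between component studies, but names none on later surgery or on type of loss.

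**Exposure.** The Dependent Variables section says "we assume the results for the first hearing assessment of a child, at any age, are representative of the long-term hearing level for that child", and concedes that "a proportion of children may not be tested until after the outcome event for the study". The Remote Hearing Assessment Dataset section gives the age range: records exist "for over 8000 children and young people aged between 0 and 21 years".

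**Type of loss.** The same dataset section says the outreach program uses audiometry to "determine the type (sensorineural, conductive, mixed, or indeterminate) and level of hearing loss". The HI variable, which serves every component study, uses degree only. Its top category is "Moderate-or-worse HI: moderate-or-worse hearing loss in the better hearing ear".

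**Target.** The five hypotheses under Objectives speak of HI without naming a cause. The abstract's conclusion says: "This study will provide first evidence of the impact of OM-related HI on the developmental, educational, and social outcomes".

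**The concern.** There are two separate mismatches, both in the exposure variable common to all five component studies.

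1. The plan accepts that OM surgery changes what a hearing result means, but guards only the years before age 4. For anyone operated on later and first tested after that, the recorded level is post-surgical. It need not represent the child's hearing in the years before the operation, and this is what the long-term assumption requires. Normal hearing is the reference category in every regression, so an error there enters every contrast.

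2. The exposure groups mix conductive, sensorineural, mixed and indeterminate loss. A contrast between such groups estimates an association with HI of any cause. Calling it evidence on OM-related HI attributes to OM something the analysis has not separated out, and the stated use of the findings is policy and resource allocation.

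**Working it through.** The article gives no sample size, event count, surgery frequency or distribution of type for this point, so there is no figure to reproduce. The check has three parts.

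**Step 1: follow one child through the rules.** Take a child with an AEDC assessment at about 5, OM surgery at 6 and a first test at 7 that is normal in both ears.

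- Surgical exclusion: not triggered, because 6 is not below 4.
- Exposure: normal hearing, from the test at 7.
- Role: reference group. If the child was impaired before surgery, the AEDC result at 5 is compared as that of a normally hearing child.

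Nothing in the text removes or flags this child.

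**Step 2: can first tests fall after age 4 often enough to matter?** The upper age is 21, so a test can follow the cut-off by up to 21 − 4 = 17 years. Hearing records start in 2007. A child sitting Year 3 NAPLAN in year Y at about age 8 was born around Y − 8, so the youngest possible age at a recorded test is about 2007 − (Y − 8) = 2015 − Y.

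| NAPLAN year | Youngest age at a recorded test |
|---|---|
| 2008 | about 7 |
| 2009 | about 6 |
| 2010 | about 5 |
| 2011 | about 4 |

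For these NAPLAN years, essentially every first recorded test falls at or after the cut-off. Likewise, any child in the youth offending study born before 2003 was at least about 4 when recording began. This shows that the window is open. It does not show how many children had surgery inside it.

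**Step 3: scale, under assumed inputs.** Let

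- f = share of the normal-hearing group that was impaired, carries the full effect, and was restored by surgery at age 4 or later but before the first test;
- s = share of the impaired group whose loss is not OM-related;
- r = effect of that loss relative to OM-related loss.

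On a linear scale the reference mean shifts by f times the true contrast, and the impaired mean becomes (1 − s) + s·r times it. So

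observed / true OM-related contrast = (1 − s) + s·r − f.

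| f | s | r | Observed / true |
|---|---|---|---|
| 2% | 0 | – | 98% |
| 5% | 0 | – | 95% |
| 10% | 0 | – | 90% |
| 0 | 5% | 0.5 | 97.5% |
| 0 | 5% | 2 | 105% |
| 0 | 5% | 3 | 110% |
| 0 | 10% | 3 | 120% |
| 10% | 10% | 0.5 | 85% |
| 10% | 10% | 3 | 110% |

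For example, the 85% row is 0.90 + 0.10 × 0.5 − 0.10 = 0.85.

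Surgery need not restore hearing fully. If it moves a child from moderate-or-worse to mild, the mild contrast takes the same form as the type term. With 5% such children carrying twice the mild effect, it is 0.95 + 0.05 × 2 = 105% of its true value, away from zero. The formula is for linear outcomes and is only a rough guide for the logistic and Cox models.

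**The case against.** The case against has four parts.

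- **The target is HI.** The objective, all five hypotheses and the discussion concern HI, and the discussion presents the direct use of HI in place of OM as a strength. Pooling types fits that aim. This stands. A reader might infer that the study set out to isolate untreated OM-related impairment and failed. The documents do not support that: no section sets such a target, and the OM-related wording sits in the background and the abstract's conclusion, not in the hypotheses or the closing conclusions. Redefining the primary exposure as conductive loss would change the hypotheses.
- **The age-4 rule has a reason.** It addresses surgery in early childhood, ahead of the earliest school outcome at about 5, and a child operated on later still had the early exposure. This justifies keeping the rule. It does not repair the exposure measurement, because that child's early impairment is what a post-surgical test can miss.
- **The limitations are declared.** The long-term assumption is stated openly, further criteria may follow in component studies, and each study will discuss bias. None of this names later surgery or type of loss, and discussion without an analysis would not show whether the results depend on them.
- **Excluding all surgery before the test has its own bias.** Where the test follows the outcome, such a filter selects on events after the outcome. A child operated on at 12 and tested at 14 would be dropped from an analysis of an outcome at 5 to 8. Late-tested children have a longer window in which to be excluded, and operated children correctly classed as impaired would go too. This stands, and it is why the filter belongs in a sensitivity analysis.

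**Conclusion.** The point holds in two limited parts. The surgery rule and the exposure rule do not fit together: a child with OM surgery at age 4 or later and a first test after it is classed on post-surgical hearing, contrary to the assumption that this test represents long-term hearing. And the exposure as defined supports conclusions on HI of any cause, not on OM-related HI.

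The size is unknown. With f and s up to 10% and r from 0.5 to 3, a contrast ranges from 85% (f = 10%, s = 10%, r = 0.5) to 120% (f = 0, s = 10%, r = 3) of its true value. All three inputs are assumptions.

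Two stronger readings are tempting. One is that every HI contrast is diluted. Full restoration to normal hearing does pull contrasts towards zero, but partial restoration can push the mild or unilateral contrast the other way. The other is that non-OM loss gathers in the moderate-or-worse group and inflates the top of the dose-response. The documents give no distribution of type by degree and no relative effect, and with r below 1 the direction reverses. The case is for a check and a change of wording, not for a new primary cohort or exposure.

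**What to change.** 1. Keep the age-4 exclusion, the HI categories and the hypotheses as the primary analysis.
2. Flag each child with a Table 1 diagnosis-plus-procedure admission before the first hearing test, and repeat each component analysis without them as a sensitivity analysis. Report by HI category how many are removed, and in how many the surgery or the test falls after the outcome, since there the exclusion selects on later events.
3. Repeat each analysis with sensorineural and mixed losses excluded, keeping conductive and indeterminate loss, with a stated rule for a child whose ears differ in type.
4. Word the conclusion as HI of any cause, in line with the hypotheses, unless the type-restricted analysis supports the OM-related wording.

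The cost is small: two further filters and somewhat lower precision in the sensitivity analyses. This assumes that the linked hospital records reach ages beyond 4 and that the type of loss is in the extract supplied. The article links the hospital dataset and says the type is determined, but does not state the hospital data years or list the supplied variables.
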